#### Proposed Statistical Analyses

We will examine the distribution of baseline covariates selected a priori (eg, age, race, clinical stage, body mass index, time since diagnosis, treatments received, current stage, and education level), overall and by group assignment. We will compute the time to enroll and proportions retained in the study (defined as completing at least one follow-up survey), overall and by arm, at 3 and 6 months. We will compare the dropout rates overall and across arms using chi-square or Fisher exact tests, as appropriate. Secondarily, we will examine the exercise and diet behavior data at baseline and 3 months for each study arm using descriptive statistics, such as means, medians, and interquartile range, and compare across arms using *t* tests and Wilcoxon rank sum tests. We will undertake an intent-to-treat analysis. We will also examine responses to the 6-month survey to explore retention and possible maintenance of behavior changes in longer term.

Our primary outcomes of this pilot RCT are accrual and participant retention. We will summarize eligibility, accrual, and retention using descriptive statistics and explore whether these factors differ by sociodemographic (ie, age, race/ethnicity, marital status, and employment) variables. In addition, we will examine adherence using the metrics described above (outcomes), overall and by randomization group.

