### Outcome Measures

We will evaluate acceptability and feasibility of the Community of Wellness intervention after 3 months via surveys, usage analytics from the Web portal, and focus groups. We will also assess study retention percentage of participants completing surveys) at 3 and 6 months as a reflection of acceptability and feasibility. Secondarily, we will explore the effectiveness of the different levels of the intervention on self-reported changes in diet or physical activity habits, QoL, and self-efficacy after 3 months and 6 months. To describe characteristics of our sample, we also ask men to self-report sociodemographic information (ie, age, race/ethnicity, marital, and employment status) and their cancer and health histories using an in-house questionnaire designed for this study.

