#### Acceptability and Feasibility

To assess acceptability and feasibility of the Web-based intervention levels, we will evaluate accrual, participant retention, and adherence. We will measure accrual as the percentage of the target sample enrolled within a 1-year recruitment period. We expect to enroll the full sample (n=200) within this time frame. We will also collect information to allow us to determine the feasibility of recruitment, for example, percentage of men eligible and percentage of men enrolled out of the total contacted about the study. We will measure retention as the percentage of participants who complete postintervention and postfollow-up surveys out of the total sample. We expect to retain 80% of the full sample postintervention (n=160) and 80% of the postintervention sample (n=128) at follow-up. We will measure adherence as the number of times a man accesses the Web portal during the intervention period (quantified as the number of log-ins). We expect 100% of men to adhere to a single log-in and that the number of log-ins will significantly differ across levels, with Level 1 having the lowest and Level 4 having the highest adherence. We will measure the technical usage statistics for the Web portal, including frequency of log-ins, individual page views, and access of exercise videos. Post intervention, participants in each level are also asked to assess their use and the helpfulness of the Web portal, its components, and other study tools through an online survey.

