### Statistical Considerations

#### Statistical Power

The primary outcomes for this pilot are acceptability and feasibility, as assessed by percent accrued in 1 year, percent recruited out of total contacted, and retention at 3 months. We anticipate enrolling 100% of the target 200 in 1 year, enrolling 3% of the total sample contacted via mass mailings, and retaining 80% of participants at 3 months. With 200 participants, we will be able to identify a retention proportion of 80% at 3 months (95% CI limits 74.5%-85.5%) and should be able to identify the other more extreme proportions with higher precision and tighter confidence limits. We will also assess the proportion completing surveys at 6 months, secondarily. If we assume 160 individuals complete the 3-month surveys, then we will have 80% power to detect a retention proportion at 6 months of 80% with a 95% confidence limit of 73.8% to 86.2%.

For the secondary outcome of behavior change, we will compute a composite *behavior score* at baseline and 3 months based on the self-reported survey data and as described above. With 50 participants per group, there is 80% of power to detect an effect size of 0.57 at a 2-sided alpha of .05 when comparing the change in score from baseline to 3 months for an intervention group (either Levels 2, 3, or 4) compared with the reference group (Level 1). For example, assuming on average men in the reference group (Level 1) experience a 2-point increase in scores from baseline to 3 months, 50 participants in Level 1 and 50 participants in Level 2 would provide power of 80% or higher if there is an average increase of 4.85 points or greater in Level 2, with an SD of 5. As a pilot study, multiple testing adjustments were not accounted for.

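### Retention is defined inconsistently: the one-survey rule cannot show loss between months 3 and 6, and a 6-month precision statement is labelled as power

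*Protocol article*

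**What the plan says.** All the relevant text is in the Methods of the protocol article.

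- **Outcome Measures** describes retention as the "percentage of participants completing surveys) at 3 and 6 months as a reflection of acceptability and feasibility".
- **Acceptability and Feasibility** gives the measure: "We will measure retention as the percentage of participants who complete postintervention and postfollow-up surveys out of the total sample". The next sentence gives the expectation: "We expect to retain 80% of the full sample postintervention (n=160) and 80% of the postintervention sample (n=128) at follow-up".
- **Statistical Power** lists the primary outcomes as "percent accrued in 1 year, percent recruited out of total contacted, and retention at 3 months" and then adds: "We will also assess the proportion completing surveys at 6 months, secondarily". Assuming 160 men complete at 3 months, it states that "we will have 80% power to detect a retention proportion at 6 months of 80% with a 95% confidence limit of 73.8% to 86.2" percent.
- **Proposed Statistical Analyses** will compute "proportions retained in the study (defined as completing at least one follow-up survey), overall and by arm, at 3 and 6 months". The sentence after it compares dropout rates overall and across arms and gives no separate definition of dropout. The next paragraph says: "Our primary outcomes of this pilot RCT are accrual and participant retention". It attaches no time point.

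**The concern.** Three rules for one quantity stand side by side: a proportion of all men enrolled, a proportion of those who completed at 3 months, and a rule that counts a man as retained once he has returned any follow-up survey.

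The third rule causes the most trouble. On its plain reading it is cumulative. A man who answered at month 3 has met it for good, so the proportion retained at month 6 cannot be lower than at month 3, however many men stop responding. A comparison of dropout by arm that uses the same rule would miss differential loss after the intervention ends. Without a date, the rule also lets a man who missed month 3 but answered at month 6 count as retained.

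Retention is a headline result of a feasibility pilot meant to identify which level of support to take forward. If the rule is left open, the 6-month figure depends on which section the analyst follows.

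The Statistical Power section also attaches a power to a confidence interval without naming any value to be tested against.

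**Working it through.** **Inputs.** 200 men randomised, 50 per arm; 160 expected to complete at 3 months (80% of 200); 128 expected at 6 months (80% of 160). All are from Acceptability and Feasibility and Statistical Power.

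**1. Reproduce the stated intervals.** Wald: p ± 1.96 × √(p(1−p)/n).

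- 3 months: 0.80 ± 1.96 × √(0.16/200) = 74.46% to 85.54%. The plan states 74.5% to 85.5%, so it reproduces.
- 6 months, n = 160: 0.80 ± 1.96 × √(0.16/160) = 73.80% to 86.20%. The plan states 73.8% to 86.2%, so it reproduces. Wilson (73.1% to 85.5%) and Clopper-Pearson (73.0% to 85.9%) do not match. The plan therefore used a Wald interval among the 160 completers.

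**2. Six-month retention under each rule, in the plan's own scenario.**

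| Rule | Calculation | Result |
|---|---|---|
| Total-sample denominator | 128/200 | 64% |
| Conditional on 3-month completion | 128/160 | 80% |
| At least one follow-up survey, cumulative | at least 160/200 | 80% or more |

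Interval for the first row: 0.64 ± 1.96 × √(0.64 × 0.36/200) = 0.64 ± 0.0665, or 57.3% to 70.7%.

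Suppose a further *a* men answer only at month 6 (the plan gives no such figure). The cumulative rule then gives (160 + a)/200: 82.5% for a = 5 and 90% for a = 20. Completion of the month-6 survey gives (128 + a)/200. The gap stays at 32/200 = 16 percentage points whatever *a* is.

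**3. By arm (assumed counts, for illustration).** Two arms of 50 each have 40 completers at month 3. At month 6, 40 of these men respond in one arm and 20 in the other, and nobody responds only at month 6. The cumulative rule scores both arms 40/50 = 80%. Month-6 completion gives 80% against 40%: pooled proportion 0.60, SE = √(0.6 × 0.4 × 2/50) = 0.098, z = 0.40/0.098 ≈ 4.1. The cumulative rule cannot show this difference.

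**4. The 80% power.** A power needs a null value p0, and none is stated. As a check, take the interval limits as nulls, with n = 160, true p = 0.80 and power = Φ[(|0.80 − p0| − z√(p0(1−p0)/160)) / √(0.16/160)].

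| p0 | Two-sided 5%, null variance | Two-sided 5%, alternative variance | One-sided 5%, null variance |
|---|---|---|---|
| 0.738 | 42% | 50% | 56% |
| 0.862 | 61% | 50% | 71% |

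None of these is 80%. A null near 0.70 would give 82%, but the document never mentions such a value. The sentence describes precision.

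**The case against.** The strongest reply is that the primary outcome is untouched, and this stands. Statistical Power dates the primary outcome at 3 months and makes 6-month completion secondary. Only one follow-up assessment exists at month 3, so the definitions agree there if retention is assessed then. A reader might infer that the primary result is compromised. That would follow only if the undated sentence in Proposed Statistical Analyses overrode the explicit time point in Statistical Power.

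The one-survey rule can also be read differently. Several questionnaires are used at each time point and the article often writes of surveys in the plural, so the rule could mean at least one questionnaire returned at that visit. Retention could then fall. The reading is possible, but the text does not say it, and the same section refers to the 6-month survey in the singular. The ambiguity needs to be settled.

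Three further inferences go too far.

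- *That the 6-month interval is miscalculated.* The condition on 160 completers is stated openly and the arithmetic is right. That 64% falls outside 73.8% to 86.2% shows only that these are two different proportions.
- *That 6-month dropout would go unreported.* Outcome Measures, Statistical Power and Proposed Statistical Analyses each plan to look at 6-month survey completion or responses. That the arm comparison of dropout uses the one-survey rule is itself an inference, though no other definition is offered.
- *That the true power is about 55%.* With 160 men and true retention of 80%, the chance that the Wald half-width is no more than 6.2 points is 0.547. That is essentially the chance of reaching the expected count of 128, which is near one half by construction. It is not a corrected power, because no test is defined.

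The article also ties no progression threshold to 6-month retention, so a specific wrong scale-up decision cannot be shown.

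**Conclusion.** The inconsistency is real and should be corrected, but it concerns 6-month retention, its comparison by arm, and the undated statement of the primary outcome. In the plan's own scenario the sections allow 64%, 80%, or 80% and above for the same 6-month result, and the cumulative rule exceeds month-6 completion among all randomised men by 16 points. This rests on the expected counts of 160 and 128 and on the cumulative reading of the one-survey rule, which is the plain reading but not the only possible one. The primary 3-month expectation (160/200, 74.5% to 85.5%) stands. The interval of 73.8% to 86.2% stands as a conditional proportion. The 80% power claim does not stand; taken alone, it would be a minor wording error.

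**What to change.** - Define retention at month t as the number completing the month-t survey divided by all men randomised (200 overall, 50 per arm), for both months. Use it in Outcome Measures, Acceptability and Feasibility, and Proposed Statistical Analyses, and for the dropout comparison across arms.
- In Proposed Statistical Analyses, state that the primary retention outcome is at 3 months, as Statistical Power already does.
- Give the expected 6-month figure as 128/200 = 64% (Wald 95% CI 57.3% to 70.7%). Keep 128/160 = 80% (73.8% to 86.2%) only if it is labelled as conditional on 3-month completion.
- Delete the 80% power wording and present the 6-month interval as precision, as the 3-month sentence does.

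The cost is wording only: no new data, participants or analyses. The expected 6-month figure becomes less favourable.

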## Results

Development of the Community of Wellness website is complete, has been beta-tested, and is currently being evaluated in the RCT. This RCT is open for enrollment (ClinicalTrials.gov NCT03406013) and anticipates completing enrollment by the end of 2018. Recruitment is open at 3 of the 4 academic medical centers (OHSU, UCSF, UC Denver, and Emory University [pending]) with the target population of 50 men enrolled at each site for a total of 200 subjects. OHSU achieved their recruitment goal and enrolled 50 men. UCSF is actively recruiting, with 27 men currently enrolled, and UC Denver is just open. We expect to fully accrue to the trial by January 2019, with final data collection complete by July 2019.

## Discussion

We have developed a tailored, self-directed, and scalable Web-based intervention accessible via computer, tablet, or phone to promote lifestyle behaviors associated with better QoL and reduced risk of cancer recurrence/progression for men with prostate cancer. Although there are many general informational websites for cancer patients [77], the study Web portal provides a variety of tools and resources to empower prostate cancer survivors to improve their physical, emotional, and mental health, including tailored exercise and diet recommendations, contemporary technology-based support tools, and health coaching. A recent meta-analysis identified 15 internet-based programs that delivered a lifestyle-based (ie, physical activity and/or diet) intervention in cancer survivors [53]. An overall positive effect was found for increasing physical activity and reducing body mass index, but findings were mixed or inconclusive for cancer treatment–related symptoms, QoL, self-efficacy, and dietary change. Only 3 programs included, but were not specific to, men with prostate cancer. Thus, it is not known whether a Web-based program that delivers both exercise and diet advice and provides multiple levels of behavior change support is feasible, acceptable, and shows preliminary efficacy to improve diet and physical activity behaviors in prostate cancer survivors.

Although the internet is an increasingly common approach to building scalable programs for behavioral interventions, it remains unclear how Web-based programs should be designed to achieve the intended goal of behavior change. This pilot RCT will address this gap in our knowledge. We will determine the acceptability and feasibility, and estimate the effect on behavior, of 4 additive levels of Web-based tools, from Web-based information (Level 1) + personalized exercise and diet recommendations and training plans (Level 2) + text messages, a physical activity tracker (Level 3) + 1 phone counseling session with an exercise trainer and 1 session with a dietician (Level 4). A trade-off to adding tools is the resources required to implement and sustain them in an ever-changing technology environment. A purely technology-based program may also lack the interpersonal contact, which might be an important component for behavior change in men with prostate cancer [53]. Thus, in comparison with a control level of static educational content on physical activity and diet, this study will systematically evaluate layers of additional support for changing physical activity and diet behavior. Depending on the outcomes from our pilot, future research may include further optimizing of the Web portal using the Multiphase Optimization Strategy framework to identify which components of the intervention are driving behavior change and SMART (Sequential, Multiple Assignment, Randomized Trial) trial designs to determine how to optimally tailor these to the varying needs of men with prostate cancer [78].

## Abbreviations

CHAMPS: Community Healthy Activities Model Program for Seniors
FFQ: food frequency questionnaire
QoL: quality of life
RCT: randomized controlled trial
UCSF: University of California, San Francisco
